**Primary Outcome**		
Sexual functioning	FSFI [36, 45]	• Assesses overall sexual functioning • 19 items; 5- and 6-point Likert scales • Subscales: sexual desire; arousal; lubrication; orgasm; satisfaction; pain • Total score*: 2-36/Subscale scores*: desire 1.2-6; arousal 0-6; lubrication 0-6; orgasm 0-6; satisfaction 0-6. Higher score indicates better overall sexual functioning. A subscale score of 0 indicates no sexual activity • Time frame: past 4 weeks • Cronbach’s alpha in a gynaecologic cancer survivors group: total score: α = 0.94; subscale scores: 0.85 ≤ α ≤ 0.94 [46] • We added 4 items (6- and 7-point Likert scales) to assess the average frequency and amount of pleasure experienced during sexual activity without sexual intercourse and sexual activity with sexual intercourse • As our study sample consists of partnered as well as unpartnered women, we added an answer option ‘not applicable, no partner’ to the two items concerning the partner relationship
**Secondary Outcomes**		
Credibility of analogue therapy rationales	CEQ [47]	• Assesses the credibility of the rationales and procedures of the intervention and the optimal CAU control group • 4 items; 9-point Likert scale • Subscales: credibility; 1 single item (expectancy) • Cronbach’s alpha: credibility subscale: 0.81 ≤ α ≤ 0.86 [48]
Generic health-related quality of life related to gynaecological cancer	EORTC QLQ-C30 [41]	• Assesses QoL of cancer patients • 30 items; 4- and 7-point Likert scales • Subscales: 5 function subscales: physical; role; emotional; cognitive; social and 3 symptom subscales: fatigue; nausea/vomiting; pain. Single items: dyspnoea; sleep disturbance; appetite loss; constipation; diarrhoea; financial impact. One global QoL scale • Subscale scores: 0-100. Higher score indicates higher level of functioning (for the function subscales) and greater degree of symptoms (for symptom subscales and/or single items) • Time frame: past week • Cronbach’s alpha: subscales: 0.54 ≤ α ≤ 0.86 [41]
Vaginal symptoms and body image concerns	EORTC QLQ-CX24 [37]	• Assesses disease-specific and treatment-specific aspects of QoL in patients with cervical cancer • 24 items; 4-point Likert scale • Subscales: symptom experience; body image; sexual/vaginal functioning. Single-items: lymphedema; peripheral neuropathy; menopausal symptoms; sexual worry; sexual activity; sexual enjoyment • Subscale score: 0-100. Higher score indicates better level of functioning (for items regarding sexual activity and sexual enjoyment) and higher level of symptoms (for all other items and scales) • Time frame: past week (for the subscales and single-items lymphedema, peripheral neuropathy and menopausal symptoms); past 4 weeks (for the single-items sexual worry, sexual activity and sexual enjoyment) • Cronbach’s alpha: subscales: 0.72 ≤ α ≤ 0.87 [37]
Urological and gastrointestinal symptoms and sexual interest	EORTC QLQ-EN24 [42]	• Assesses urological and gastrointestinal symptoms, and sexual functioning • 10 items^#^; 4-point Likert scale • Subscales: urological symptoms; gastrointestinal symptoms. Single-item: sexual interest • Subscale score: 0-100. Higher score indicates higher level of urological and gastrointestinal symptoms and higher sexual interest • Time frame: past week • Cronbach’s alpha: subscales: 0.74 ≤ α ≤ 0.75 [42]
Quality of life	EQ-5D-5 L [49, 50]]	• Assesses (general) health • 5 items; 5-point Likert scale & Visual Analogue Scale (VAS) • 5 dimensions: mobility; self-care; usual activities; pain/discomfort; anxiety/depression. One VAS for general health • Time frame: today
Sexual distress	FSDS [39, 45]	• Assesses distress related to sexual dysfunction • 12 items; 5-point Likert scale • Total score: 0-48. Higher score indicates higher level of sexual distress • Time frame: past 30 days • Cronbach’s alpha: 0.86 ≤ α ≤ 0.94 [39]
Fear of coital and non-coital sexual activity	FSQ [38]	• Assesses aspects of fear of sexuality • 8 items; 5-point Likert scale • Subscales: fear of non-penetration sexual activity; fear of coitus/vaginal penetration • Subscale scores: fear of non-coital sexual activity 0-20; fear of coitus 0-12. Higher score indicates higher fear • Cronbach’s alpha: 0.82 ≤ α ≤ 0.86 [38]
Psychological distress	HADS [43, 51]]	• Assesses psychological distress • 14 items; 4 point Likert scale • Subscales: depression (HADS-D); anxiety (HADS-A) • Total score: 0-42/Subscale scores: 0-21. Higher score indicates more psychological distress • Time frame: past week • Cronbach’s alpha: HADS-D: 0.67 ≤ α ≤ 0.90; HADS-A: 0.68 ≤ α ≤ 0.93 [52]
Gynaecological cancer treatment related distress	IES [REF Brom, 1985; [40, 53]	• Assesses current treatment related distress • 15 items; 4-point scale • Subscales: intrusion; avoidance • Total score: 0-75/Subscale scores: intrusion 0-35; avoidance 0-40. Higher score indicates: higher tendency to be triggered by stimuli associated with the traumatic event(s) (for items regarding intrusion); higher tendency to avoid situations that are reminders of the treatment (for items regarding avoidance) • Time frame: past week • Cronbach’s alpha: total score: 0.87 ≤ α ≤ 0.96; intrusion subscale: 0.85 ≤ α ≤ 0.95; avoidance subscale: 0.77 ≤ α ≤ 0.91 [53]
Relationship dissatisfaction	MMQ Marital scale [44, 54]	• Assesses marital dissatisfaction • 10 items; 9-point Likert scale (range 0-8) • Total scale-score: 0-80. Higher score indicates higher marital dissatisfaction • Time frame: past 2 weeks • Cronbach’s alpha in non-distressed group: 0.87 ≤ α ≤ 0.88 [54]

*The score is calculated based on weighted items

^#^Due to the overlap between 4 items from the QLQ-EN24 and QLQ-CX24, we only included the remaining 6 items

CAU = Care as usual; CEQ = Credibility/Expectancy Questionnaire; EORTC QLQ-C30 = European Organization for Research and Treatment of Cancer Quality of Life Questionnaire-Core 30; EORTC QLQ-CX24 = European Organization for Research and Treatment of Cancer Quality of Life Questionnaire-Gynaecological Cancer Module; EORTC QLQ-EN24 = European Organization for Research and Treatment of Cancer Quality of Life Questionnaire-Endometrial Cancer Module; EQ-5D-5 L = EuroQol 5D-5 L; FSDS = Female Sexual Distress Scale; FSFI = Female Sexual Function Index; FSQ = Fear of Sexuality Questionnaire; HADS = Hospital Anxiety and Depression Scale; IES = Impact of Event Scale; MMQ = Maudsley Marital Questionnaire; QoL = Quality of Life

Additionally, the secondary outcome measures include a 4-item questionnaire for women treated with EBRT+BT regarding the frequency of dilator use: (1) ‘How often have you used the dilator in the past month?’, (2) ‘Which size(s) dilator(s) did you use?’, (3) ‘How often did you have other kinds of penetration (including penile penetration) in the past month?’, and (4) ‘How often did you use petroleum jelly (Vaseline) tampons?’.

Furthermore, the following vaginal symptoms are assessed by standardized clinical examination for all participants: dryness, shortening/tightening, mucositis, discharge, blood loss, fibrosis, atrophy, pain, length (in millimetre) and dyspareunia. Vaginal symptoms will be recorded using the Common Terminology Criteria Sexual rehabilitation after RT for gynaecological cancers for Adverse Events (CTCAE), version 4.037.

#### Cost-effectiveness

A cost-effectiveness analysis (CEA) will be conducted in which the costs of the intervention will be related to shifts in other health care costs and the impact on patient outcome. A cost-price analysis will be performed for the nurse-led sexual rehabilitation intervention (including training, counselling hours and materials). Other healthcare use will be limited to sexuality-related health care utilization (including gynaecologist, radiation oncologist, general practitioner, psychologist and sexologist) and medication use, estimated from patient reports and valued using standard prices.

Estimated costs will be related to the impact on the number of women with sexual improvement after 12 months (costs-per-improved-patient, defined as a Reliable Change Index (RCI) [55] >1.96 on the FSFI [36] total score) and to the impact on quality-adjusted life years (cost-per-QALYs). In the primary analysis, consistent with Dutch guidelines, QALYs will be calculated using the Dutch tariff for the 5-level EuroQol-5D (EQ-5D-5 L) [49, 50, 56]. As a secondary analysis, QALYs will also be estimated using the EuroQol visual analogue scale (EQ-VAS, with power transformation) as predicted by a mapping from the FSFI to the EQ-VAS. This secondary analysis is included because the Dutch tariff for the EQ-5D-5 L does not explicitly value sexuality and mapping from the FSFI will make the approach more sensitive to change.

#### Other study parameters

In addition to treatment- and patient characteristics, treatment credibility and expectancy for improvement will be assessed using the 4-item Credibility and Expectancy Questionnaire (CEQ) [47]. These parameters will be measured at T3. Additionally, at T2-T5 all women will be requested to report the use of any counselling or therapy in the course of their rehabilitation period. Furthermore, the type (face-to-face or by telephone) and the duration of the session, and modules used during the session are documented by the oncology nurses in CRFs. Finally, for each participant, the date of the completion of study participation and the reason for ending study participation are registered in web-based CRFs.

### Statistical methods

#### Power and sample size calculation

The FSFI [36] is the primary outcome measure on which sample size calculations are based. With a total sample of 128 women (64 per group), and under the assumption of no interaction, the study will have a 80% power to detect a 0.5 standard deviation difference (Cohen’s effect size [57]) for the main effects of the sexual rehabilitation intervention, with the p-value set at 0.05 (two-sided test). Based on our pilot study we expect an attrition rate of 40% (i.e., women who discontinue participation in the study due to somatic reasons such as cancer recurrence) [32]. Consequently, we have to include at least 107 women in both study groups ultimately resulting in an intended sample size of 220 women [57].

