## Abstract

**Background:**

Sexual problems are frequently reported after treatment with radiotherapy (RT) for gynaecological cancer (GC), in particular after combined external beam radiotherapy and brachytherapy (EBRT+BT). Studies demonstrate that psychosexual support should include cognitive behavioural interventions and involvement of the patient’s partner, if available. Therefore, we developed a nurse-led sexual rehabilitation intervention, including these key components. The intervention was previously pilot-tested and results demonstrated that this intervention improves women’s sexual functioning and increases dilator compliance. The objective of the current study is to investigate the (cost-)effectiveness of the intervention compared to optimal care as usual (CAU). We expect that women who receive the intervention will report a statistically significant greater improvement in sexual functioning and – for women who receive EBRT+BT – higher compliance with dilator use, from baseline to 12 months post-RT than women who receive optimal care as usual (CAU).

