#### Intervention group: the nurse-led sexual rehabilitation intervention

The intervention consists of four one-hour face-to-face sessions at 1, 3, 6, and 12 months post-RT. These sessions are planned synchronously with women’s radiation oncologist follow-up visits. An additional session is scheduled for women who received EBRT+BT at 2 months, during which potential barriers and problems with dilator use are discussed. Furthermore, if preferred, an extra follow-up session/telephone consultation of 30 min can be scheduled between 6 and 12 months after RT. If a woman is in a relationship, the partner is invited to accompany her in the sessions.

The sexual rehabilitation intervention consists of 11 modules. A description of the content of the modules is provided in Table 1. The modules include topics such as education regarding the specific cancer diagnosis and treatment, education on the importance of regular use of vaginal dilators (if applicable), discussing potential experienced barriers to dilator use (if applicable) and lubricant use, fear of penetration with dilators (if applicable) and fear of resuming sexual activity after cancer, promoting couples’ mutual coping and support processes and addressing sexual and body image concerns. The content of the intervention is a personalized programme tailored to the participant-specific psychological, relational and somatic factors. During a session, the oncology nurse selects the specific module(s) that fits the woman’s (and her partner’s) needs. The decision tree for module selection is provided in Fig. 2.

**Table 1 Tab1:** Description of the sexual rehabilitation intervention modules

**Module 1: Brief sexual history**	This module describes how the nurse can question the patient in-depth about sexual problems on various domains of sexual functioning, including sexual interest/arousal, orgasm, pain and sexual satisfaction. It also covers psycho-education about sexuality and the sexual response curve [33] and provides information about frequently occurring sexual problems and solutions.
**Module 2: Pain during intercourse**	This module includes practical guidelines that the nurse can provide regarding pain during intercourse after radiotherapy-, with referrals to module 3, 4, 6 and 7, and explains how to provide psycho-education about the circular model of dyspareunia [34], which is based on a cognitive behavioural framework.

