### Statistical analysis

T-tests or appropriate non-parametric statistics for independent samples will be used to evaluate the comparability of the intervention and control group at baseline in terms of sociodemographic and clinical characteristics. If, despite the stratified randomization procedure, the groups are not comparable on one or more background variables, those variables will be employed routinely as covariates in subsequent analyses.

Questionnaire scores will be calculated according to published scoring algorithms. Differences in changes in the primary outcome measure and secondary outcome measures between groups (intervention vs. control group) over time (T1-T5) will be evaluated using multilevel models and are based on an intention-to-treat approach. Effect sizes will be calculated using standard statistical procedures.

Furthermore, multilevel models will be used to investigate if improvement in sexual functioning in the intervention group is moderated by treatment/cancer characteristics and patient characteristics or mediated by e.g. sexual symptoms and vaginal symptoms or frequency of dilator use. Cost-effectiveness will be analysed using net benefit analysis, with multiple imputation to account for missing data.

Per protocol analyses will also be carried out (as a secondary analysis), comparing women who meet minimal compliance levels with the intervention with the control group. We will use correlation analyses to examine the relationship between degree of intervention adherence and intervention effect.

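### The 80% power is calculated for a main effect on one score per woman and is not shown to apply to the planned comparison of FSFI change over T1-T5

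*Protocol article*

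**What the plan says.** In the protocol article, 'Power and sample size calculation' states that "The FSFI [36] is the primary outcome measure on which sample size calculations are based". It takes 64 women per group, a two-sided 0.05 level and a 0.5 SD difference, and gives the condition and the power together: "under the assumption of no interaction, the study will have a 80% power to detect a 0.5 standard deviation difference". The effect so powered is described as "for the main effects of the sexual rehabilitation intervention". Attrition of 40% raises the number to at least 107 per group, with 220 intended in total.

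'Statistical analysis' plans something else: "Differences in changes in the primary outcome measure and secondary outcome measures between groups (intervention vs. control group) over time (T1-T5) will be evaluated", with multilevel models and by intention to treat. T1, the questionnaire completed before randomisation, is one of the modelled time points. Covariates are mentioned only for background variables on which the groups turn out not to be comparable. Adjustment for baseline FSFI is not mentioned.

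The hypothesis in the abstract is a greater improvement "from baseline to 12 months post-RT than women who receive optimal care as usual (CAU"). The Background and the Discussion repeat it, and the Discussion also hopes for a difference at 12 months.

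**The concern.** A between-group difference in change from T1, in a model where T1 is one of the outcomes, is a group-by-time effect. A main effect of group is a different quantity. If the interaction assumed absent is group by time, the power sentence assumes away the effect that the analysis is meant to detect.

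Even if another interaction is meant, the calculation contains no baseline, no repeated measure and no correlation, so a reader cannot tell which test has 80% power. At stake are the meaning of the published power and the choice of contrast. A multilevel model over five time points can yield several intervention tests with quite different power, and 'Statistical analysis' does not say which one decides the trial.

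**Working it through.** **Inputs from the article.** 64 per group, 0.5 SD difference, two-sided 0.05, 80% power, 40% attrition, time points T1 to T5.

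**Inputs assumed.** Correlation rho between T1 and T5 FSFI of 0.2, 0.3, 0.5 and 0.7 (the article gives none); equal SD at T1 and T5; 0.5 in units of the SD of a single score; 64 women per arm contributing to the contrast.

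**Step 1: reproduce the stated figures.** Two-sample t-test, noncentrality = 0.5 × sqrt(64/2) = 2.83, 126 degrees of freedom: power 80.1%. Attrition: 64/(1 − 0.40) = 106.7, so 107 per group and 214 in total, consistent with the intended 220. The arithmetic is right, and it uses one score per woman.

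**Step 2: unadjusted change from T1 to T5.** SD of change = SD × sqrt(2(1 − rho)), so the standardised effect is 0.5/sqrt(2(1 − rho)).

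**Step 3: T5 difference adjusted for T1 FSFI.** Residual SD = SD × sqrt(1 − rho²), so the standardised effect is 0.5/sqrt(1 − rho²).

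| rho | Effect, change | Power, change | Effect, adjusted | Power, adjusted |
|---|---|---|---|---|
| 0.2 | 0.395 | 60% | 0.510 | 82% |
| 0.3 | 0.423 | 66% | 0.524 | 84% |
| 0.5 | 0.500 | 80% | 0.577 | 90% |
| 0.7 | 0.645 | 95% | 0.700 | 98% |

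The ratio of the variances is 2(1 − rho)/(1 − rho²) = 2/(1 + rho), which is 1.67 at rho 0.2 and 1.33 at rho 0.5. The unadjusted change needs that many times the sample size of the adjusted contrast for the same power.

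**Step 4: the group-by-time reading of the no-interaction condition.** A constant 0.5 SD difference at all of T1 to T5 gives zero true difference in change. A joint group-by-time test on four degrees of freedom then rejects at its 5% level only.

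**Step 5: the other reading of the SD.** If the 0.5 is in units of the SD of the FSFI change, the standardised effect of the change contrast is 0.5 whatever rho is, and 64 per group gives 80.1%.

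**The case against.** The strongest reply is that the article defines neither the interaction nor the SD. The interaction may be intervention by type of radiotherapy or by partner status, the stratification factors, or by one of the moderators that 'Statistical analysis' plans to examine. With that meaning and an SD of change, the 80% fits a difference in change (Step 5). This stands, and it is why the point is that the 80% is not shown to apply, rather than that it is wrong.

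It is also fair that 12 months is named in the hypothesis and that the exact model contrast may be in an analysis plan that is not shown. The lack of a named contrast is therefore not an error in itself. The power sentence still has to be tied to a test.

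Four stronger readings are tempting, and the article does not support them:

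- **The trial is too small.** The unadjusted change falls below 80% only when rho is under about 0.5 and the SD is that of a single score. The baseline-adjusted contrast is above 80% at every rho shown.
- **The 80% holds only near rho 0.5.** Above 0.5 the change contrast exceeds 80%, and with an SD of change rho does not matter.
- **T2 cannot carry an effect.** The intervention has "four one-hour face-to-face sessions at 1, 3, 6, and 12 months post-RT", and T2 is also at 1 month. The readable text does not give their order, and the reminder procedure lets some T2 forms come later. A small T2 effect is likely, but zero is not established.
- **The planned test is an average over T1-T5.** The power sentence speaks of main effects, but the analysis section plans differences in change, so the power of a pooled average says nothing about the planned test.

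**Conclusion.** The point holds in a limited form. The power statement describes a main effect on a single score, while the analysis and hypothesis describe a difference in change from baseline to 12 months, and nothing in the article connects the two. For a 0.5 SD effect at 12 months with 64 women per arm, power runs from 60% to 95% for the unadjusted change and from 82% to 98% for the baseline-adjusted difference, over rho 0.2 to 0.7. These ranges rest on the assumed rho, equal SDs at T1 and T5, and an SD of a single score. The planned number of women can stand. What needs correcting is the link between power and test, and adjusting for T1 FSFI is a free gain in precision.

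**What to change.** Name the between-arm difference in FSFI at T5 (12 months) as the primary contrast. Estimate it from the planned multilevel model with time as a categorical factor and T1 FSFI either constrained to equal means across arms or used as a covariate. Make the other time points secondary.

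Restate the power for that contrast, saying which SD the 0.5 refers to and which rho is assumed. With 64 per arm and an SD of a single score it is 82%, 84%, 90% and 98% at rho 0.2, 0.3, 0.5 and 0.7. Define the interaction assumed absent, or delete the no-interaction and main-effect wording.

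The cost is a revised power sentence and a few lines in the analysis section or analysis plan. No extra patients or data are needed. The change should be made before anyone sees results by arm, so that the time contrast cannot be chosen afterwards.

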### Statistical analysis

T-tests or appropriate non-parametric statistics for independent samples will be used to evaluate the comparability of the intervention and control group at baseline in terms of sociodemographic and clinical characteristics. If, despite the stratified randomization procedure, the groups are not comparable on one or more background variables, those variables will be employed routinely as covariates in subsequent analyses.

Questionnaire scores will be calculated according to published scoring algorithms. Differences in changes in the primary outcome measure and secondary outcome measures between groups (intervention vs. control group) over time (T1-T5) will be evaluated using multilevel models and are based on an intention-to-treat approach. Effect sizes will be calculated using standard statistical procedures.

Furthermore, multilevel models will be used to investigate if improvement in sexual functioning in the intervention group is moderated by treatment/cancer characteristics and patient characteristics or mediated by e.g. sexual symptoms and vaginal symptoms or frequency of dilator use. Cost-effectiveness will be analysed using net benefit analysis, with multiple imputation to account for missing data.

Per protocol analyses will also be carried out (as a secondary analysis), comparing women who meet minimal compliance levels with the intervention with the control group. We will use correlation analyses to examine the relationship between degree of intervention adherence and intervention effect.

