### Recruitment and randomization

The treating radiation oncologists screen potential participants with regard to the inclusion and exclusion criteria. Eligible women are informed about the background, rationale and specifics of the study protocol. Women who want to participate in the study provide written informed consent and complete a paper-and-pencil baseline questionnaire before randomization. After inclusion, participants are assigned a unique study identifier by the local data manager, which will be filled out on all questionnaires and used in the data files. Inclusion and randomization take place before the completion of RT. Participants are randomized to either the intervention- or the optimal CAU control group (1:1), and within each centre stratified by type of radiotherapy (EBRT+BT versus EBRT only) and having a partner (yes/no). The randomization is block stratified with varying block sizes, and is performed by the local data manager, using a secured web-based data-management system.

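### Covariates are chosen by testing the arms against each other at baseline, which selects on chance imbalance and almost never picks the stratification factors

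*Protocol article*

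**What the plan says.** The Statistical analysis section opens by comparing the arms on sociodemographic and clinical characteristics with t-tests or non-parametric tests. If, in spite of stratification, "the groups are not comparable on one or more background variables, those variables will be employed routinely as covariates in subsequent analyses". No threshold for non-comparability is given. This is the only covariate rule in the article. The primary analysis is a multilevel model of differences in change over T1 to T5, by intention to treat, and no fixed covariates are named.

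Under Recruitment and randomization, "Participants are randomized to either the intervention- or the optimal CAU control group (1:1), and within each centre stratified by type of radiotherapy" and, in the same sentence, by having a partner. With 10 centres that is up to 10 × 2 × 2 = 40 strata.

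The article regards the first two factors as relevant to the outcome. The Background says radiotherapy harms sexual functioning, most of all when EBRT and BT are combined. The Discussion gives lack of a partner as one reason for sexual inactivity, notes that 15 of the 19 FSFI items score inactivity as zero, and gives this as the reason for stratifying. It also cites variation between centres in patients and procedures.

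**The concern.** A p-value comparing randomised arms at baseline measures how unusual the chance allocation was. It does not measure whether the variable predicts the FSFI, which is what makes a covariate useful. A rule built on it has three effects:

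- The covariate set of the primary and later analyses is decided by chance. With no threshold stated, two analysts could also reach different sets.
- Factors balanced by design cannot be expected to trigger the rule. These are the factors that the design itself gives reason to adjust for.
- If balanced factors predict the analysed contrast but are left out, their variance stays in the residual, although stratification has already removed it from the treatment comparison. The model standard error is then too large.

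What is at stake is efficiency and a reproducible primary model, not a raised false-positive rate.

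**Working it through.** **1. The plan's own figure.** The Power and sample size section states "With a total sample of 128 women (64 per group") and that "the study will have a 80% power to detect a 0.5 standard deviation difference" at two-sided 0.05. The normal approximation gives n = 2(1.960 + 0.842)² / 0.5² = 62.8, so 63 per arm. The t-test version gives 63.8, so 64 per arm, with power 0.801. With 40% attrition, 64 / 0.6 = 106.7, so 107 per arm and 214 in total; 220 is intended. The figure reproduces, and this point does not affect it.

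**2. Chance of triggering the rule.** The section on sociodemographic and clinical data lists 6 sociodemographic variables and 15 clinical ones (hormone replacement counted under medication, height and weight separately). Removing relational status and type of radiotherapy as stratified leaves 21 − 2 = 19. For k independent variables at an assumed 0.05 threshold, P(at least one) = 1 − 0.95^k:

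| k | P |
|---|---|
| 10 | 40% |
| 15 | 54% |
| 19 | 62% |

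Some of the variables are clearly correlated, so the true figure differs.

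**3. Chance of selecting the stratification factors.** A simulation used 3,000 trials per setting, 10 centres × radiotherapy type × partner, and 15 other baseline variables tested at 0.05. Assumptions not in the article: blocks of 2, 4 and 6; 60% EBRT+BT; 75% partnered. Radiotherapy type and partner status each reached p < 0.05 in at most 0.5% of trials at N = 128 and at most 0.1% at N = 220.

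**4. Standard error, size and power.** The same simulation used a linear regression on one outcome, read as the change score. R² is the share of its variance explained by radiotherapy type and partner status together; the 15 other variables explain 10%. The article gives no R², so a range is shown. The first two result columns cover N = 128 and 220 under no treatment effect; power is at N = 128 and 0.5 SD.

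| R² | Mean model SE / true SD, rule | Type I error, rule | Power, rule | Power, pre-specified |
|---|---|---|---|---|
| 0 | 1.00–1.03 | 4.6–5.1% | 80% | 81% |
| 0.1 | 1.05 | 3.7–4.2% | 80% | 84% |
| 0.2 | 1.08–1.10 | 3.4% | 80% | 88% |
| 0.3 | 1.15 | 2.3–2.4% | 83% | 93% |

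Monte Carlo standard errors are about √(0.034 × 0.966 / 3000) = 0.3 points for size and √(0.8 × 0.2 / 3000) = 0.7 points for power. With pre-specified terms and no baseline testing, size is 4.4–5.6% for R² from 0.1 to 0.3.

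Closed-form check of the power gain: the noncentrality is 0.5 × √(64/2) = 2.828. Dividing by √(1 − R²) gives 2.981 (R² = 0.1) and 3.162 (R² = 0.2), so power is Φ(2.981 − 1.960) = 85% and Φ(3.162 − 1.960) = 88%, in line with the simulation.

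**5. When the factors predict level but not change.** The planned contrast is change over T1 to T5. In a simulated random-intercept model with five visits, where the two factors explained 20% of variance as stable level effects, the SE of the arm-by-T5 term was 0.1762 with and without them on complete data. With 40% dropout the two SEs were 0.1634 and 0.1624, a difference of 0.0010 / 0.1624 = 0.6%. The table in step 4 therefore applies only to the extent that the factors predict change.

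**The case against.** The strongest reply is that the article says which variables are added when the arms differ, not that nothing else is in the model. A reader might infer that the stratification factors are excluded. The text does not say so: the levels and fixed terms of the multilevel model are not listed, and an analysis plan not shown here may include them. That stands. What remains is the stated rule itself, which such a plan would have to replace rather than merely supplement.

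Second, the loss may be small. A stable level effect hardly touches a change contrast (step 5), and the partner remark in the Discussion is most naturally about level. The Background makes an effect on change plausible for radiotherapy type but gives no figure. Even in step 4 the planned 80% power is kept; only additional power is forgone. This stands and limits the size of the point.

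Third, selection uses baseline characteristics only, under a rule stated in advance, so it does not look at outcomes. That also stands: the fault is dependence on chance imbalance, not outcome-driven modelling.

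Fourth, 62% requires 19 independent tests at a threshold that the article does not give. It is an illustration under stated assumptions.

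**Conclusion.** The point holds as a flaw in the stated rule with a conservative consequence. Adjustment is decided by chance imbalance, no threshold is given, and the factors used in randomisation will almost never qualify.

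If radiotherapy type and partner status explain 10% to 20% of the variance of change, type I error falls to about 4% to 3.4%, and power is about 80% where 84% to 88% was available. If they predict only a stable level, or nothing, the effect is negligible. These figures rest on the assumed R², the 0.05 baseline threshold, the block sizes and the case mix. The simulation gave centre no effect of its own.

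Three stronger readings are not supported:

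- *Invalid standard errors with inflated false positives.* The errors are too large, not too small.
- *Baseline FSFI is left to the rule and should be added as a covariate.* T1 is already a response in the T1 to T5 model, so a separate covariate would use it twice.
- *Clustering by nurse belongs to this point.* The article gives neither the number of nurses nor an intraclass correlation, so no size can be put on it.

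**What to change.** Replace the rule in the Statistical analysis section, before data are analysed, as follows:

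- Describe baseline characteristics by arm without significance tests.
- Pre-specify type of radiotherapy, partner status and centre (fixed or random) in the primary multilevel model. Where the contrast is change, include factor-by-time terms, since main effects alone do little for it.
- Keep T1 as a response and add no separate baseline-FSFI covariate.
- Move adjustment for any other observed imbalance to a labelled sensitivity analysis.

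The cost is wording and a few model terms. If time is categorical with five visits, radiotherapy type and partner status take 2 × (1 + 4) = 10 parameters, plus centre as one variance component or 9 fixed terms. With up to 40 strata and 220 women (5.5 per stratum on average), the factors should enter separately rather than as one term per stratum. All of them are already recorded for randomisation, so no new data are needed.
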